## Abstract

**Background:**

Most people with mental health problems do not seek help, with delays of even decades in seeking professional help. Lack of engagement with professional mental health services can lead to poor outcomes and functional impairment. However, few effective interventions have been identified to improve help-seeking in adults, and those that exist are not widely implemented to deliver public health impact. Co-designing interventions with people with lived experience of mental ill-health and other relevant stakeholders is critical to increase the likelihood of uptake and engagement with these programs.

**Objective:**

This study aims to (1) test the effectiveness of a co-designed help-seeking program on increasing professional help-seeking intentions in employees in a workplace setting; (2) determine whether the program reduces mental illness stigma and improves help-seeking intentions and behavior, mental health literacy, mental health symptoms, and work and activity functioning relative to the control condition; (3) explore factors that facilitate broader implementation of the co-designed program; and (4) explore the cost-effectiveness of the co-designed program compared to the control condition over 6 months.

**Methods:**

A 2-arm cluster randomized controlled trial will be conducted (target sample: N=900 from 30 to 36 workplaces, with n=25 to 35 participants per workplace). The trial will compare the relative effectiveness of an enhanced interactive program (intervention condition) with a standard psychoeducation-alone program (active control condition) on the primary outcome of professional help-seeking intentions as measured by the General Help-Seeking Questionnaire. Secondary outcomes include the impact on mental illness stigma; mental health literacy; help-seeking attitudes and behavior; work and activity functioning; quality of life; and symptoms of mental ill-health including depression, anxiety, and general psychological distress.

**Results:**

Facilitators of and risks to the trial are identified and addressed in this protocol. Recruitment of workplaces is scheduled to commence in the first quarter of 2024.

**Conclusions:**

If effective, the program has the potential to be ready for rapid dissemination throughout Australia, with the potential to increase appropriate and efficient service use across the spectrum of evidence-based services.

**Trial Registration:**

Australian New Zealand Clinical Trials Registry (ANZCTR) ACTRN12623000270617p; https://www.anzctr.org.au/Trial/Registration/TrialReview.aspx?id=385376

**International Registered Report Identifier (IRRID):**

PRR1-10.2196/55529

## Introduction

### Background

In a 12-month period, 16.8% of Australian adults will experience an anxiety disorder and 4.6% will experience a major depressive episode [1]. Despite the high prevalence of common mental disorders, most people with a mental health problem will not seek help from a health professional [1]. Among those who seek help, delays of years or decades to seeking professional help are common [2,3]. The lack of engagement with professional services may lead to poorer outcomes in both mental health symptoms and functional impairment [4] and productivity loss [5-8]. While structural factors such as service accessibility impact help-seeking, we also know that individual factors such as the stigma of mental illness, the stigma of help-seeking, poor mental health literacy, and high self-reliance reduce the likelihood of an individual seeking help when experiencing symptoms of mental ill-health [9,10].

### Mental Health Promotion Programs

Promotion programs that are universally delivered (ie, provided to all people in a population, regardless of risk or symptom level) have the potential to improve mental health. Such programs often involve targeting key barriers to help-seeking, such as knowledge or mental health literacy (including how, where, and when to seek help), and reducing stigmatizing attitudes toward help-seeking [11]. Facilitating pathways to professional help is critical, as treatment delays from the onset of symptoms can be as long as 8 years for depression and up to 23 years for anxiety disorders, leading to potentially significant and avoidable disability [3]. Mental disorders such as depression and anxiety can follow a chronic and treatment-resistant course in the absence of early intervention [12]. Therefore, there is increasing recognition of the need for promotion and prevention approaches.

Much of the evidence for the effectiveness of universal prevention programs on knowledge and mental health outcomes comes from adolescent settings [13,14], typically showing modest effects that may have a significant impact when delivered at scale. However, >50% of anxiety disorders and 75% of mood disorders emerge in adulthood [15], and they have high rates of relapse [16]. Workplaces offer an ideal environment to deliver prevention programs due to the significant proportion of adults in paid employment and the motivation among employers to ensure their employees remain well and productive. Prevention programs for adults delivered in the workplace typically focus on reducing emerging or subthreshold symptoms of depression, anxiety, or distress, with very modest effects for universally delivered programs [17]. A promising alternative approach is to promote help-seeking for distress by increasing knowledge about mental health and pathways into care, along with reducing stigmatizing attitudes about mental ill-health [18,19]. However, very few help-seeking promotion programs have been evaluated in general adult populations, with just 2 focusing on workplaces [20] and neither being implemented broadly. Consequently, there may be untapped opportunities for developing and implementing evidence-based mental health promotion programs within workplaces that ultimately lead to greater support for adults who experience mental distress.

### Co-Design and Online Delivery Modes

The COVID-19 pandemic has dramatically accelerated the need for mental health programs [21], particularly those delivered distally [22]. However, few effective programs have been identified for improving help-seeking in adults [23], and existing interventions are not widely implemented to deliver public health impact [19,24]. Web-based mental health interventions are cost-effective [25] and can be widely disseminated [26], but they can have high dropout rates, increasing the need for co-design to improve acceptability [27]. There is increasing recognition of the expertise of people with lived experience of mental health problems in research, and the important insights end users of a product or service can bring to the research process, by improving translation, real-world impact, and responsive practice [28]. Co-design involves partnering with end users during all stages of designing and developing a product or service. Using this method enhances the potential that the service can be tailored to the target population, creating a strong potential to foster a sense of empowerment and ownership, which in turn may improve the uptake of and engagement with the service [27].

### This Study

Programs that promote help-seeking intentions and behaviors can reach large proportions of people when delivered at scale within workplaces. This paper is a protocol for a cluster randomized controlled trial (RCT) that will provide a robust evaluation of the effectiveness and cost-effectiveness of a novel co-designed program for improving help-seeking in workplaces. Furthermore, this study examines potential factors that may impede or enhance the subsequent delivery and implementation of the program.

### Aims

The aims of this study are as follows:

To test the effectiveness of a co-designed help-seeking program (the Helipad program) on increasing professional help-seeking intentions (primary outcome) in employees in a workplace setting at posttest (primary end point) and the 6-month follow-upTo determine whether the program reduces mental illness stigma and improves help-seeking attitudes and behavior, mental health literacy, mental health symptoms, quality of life, and functioning (secondary outcomes) relative to the control condition at the 6-month follow-upTo explore factors that facilitate broader implementation of the co-designed programTo explore the cost-effectiveness of the co-designed program compared to the active control condition from the health sector and societal perspectives at the 6-month follow-up

### Hypotheses

To investigate the abovementioned aims, we propose the following hypotheses.

#### Primary Hypothesis (Aim 1)

Hypothesis 1: Help-seeking intentions will be higher in the Helipad co-designed interactive program condition relative to the control condition (standard psychoeducation only) at posttest.

#### Secondary Hypotheses (Aim 2)

Hypothesis 2: Mental illness stigma will be lower and mental health literacy and help-seeking attitudes will be higher in the Helipad co-designed interactive program condition relative to the control condition (standard psychoeducation only) at posttest.Hypothesis 3: Help-seeking behavior will be greater in the Helipad co-designed interactive program condition among people with elevated symptoms of depression or anxiety relative to the control condition (standard psychoeducation only) at the 6-month follow-up.Hypothesis 4: Symptoms of mental ill-health will be lower and quality of life and functioning will be higher in the Helipad co-designed interactive program condition relative to the control condition (standard psychoeducation only) at the 6-month follow-up.

#### Exploratory Hypotheses (Aim 3)

We do not have any specific hypotheses for factors that facilitate broader implementation of the program as this is exploratory; furthermore, we will use interviews with participants to explore this aim.

#### Exploratory Hypotheses (Aim 4)

The Helipad program will be cost-effective relative to the active control (psychoeducation) at the 6-month follow-up from health sector and societal perspectives relative to the willingness-to-pay thresholds identified by the Productivity Commission report on mental health [29].

## Methods

### Trial Design

A 2-arm cluster RCT will test whether the Helipad co-designed interactive program increases help-seeking intentions in employees in workplaces more than the standard psychoeducation-alone program. Workplaces will be randomly allocated using minimization processes to either (1) the active intervention condition comprising the Helipad program or (2) an active control condition (a web-based time-matched standard psychoeducation program). Help-seeking intentions will be assessed at the individual level accounting for clustering by workplace. Self-report assessments will be conducted on the web at preintervention, immediately postintervention, and at the 6-month follow-up. This study protocol addresses the Standard Protocol Items: Recommendations for Interventional Trials (SPIRIT) checklist [30].

The flow of participants through the study is presented in Figure 1.

**Figure 1 figure1:**
[figure not shown]
Cluster randomized controlled trial flowchart for the Helipad brief workplace training program to support help seeking for mental ill-health.

### Interventions

#### The Helipad Program

A co-design working group was convened to develop the program from May to October 2023. Two authors, who identify as lived experience researchers (AG and CH), facilitated and led the co-design working group. The program was developed using principles of community-based co-design research, which are particularly appropriate in implementation research that focuses on the relevance and uptake of interventions within and across organizations [31]. The co-design group comprised 9 team members from the community. In addition, 2 web development team members were consulted during the later stages of the co-design working group’s activities. All 9 community co-design team members were currently employed, and almost all identified as belonging to >1 group (consumers: 6/9, 67%; carers: 5/9, 56%; managers: 2/9, 22%; human resources staff: 2/9, 22%; and clinician: 1/9, 11%). The co-design process is outlined in detail in a separate paper ([name] et al, forthcoming).

The resulting co-designed program, called Helipad, is brief and takes approximately 20 minutes to complete. Brevity was essential to ensure that the information provided could be easily digestible and did not form a barrier to completing the program.

The Helipad program consists of 5 interactive modules addressing the core issues described by the co-design group as being important to facilitating help-seeking in workplaces (Textbox 1). The modules have been designed to be highly interactive, including clickable diagrams, videos of health professionals and people with lived experience, and interactive quizzes.

Interactive modules of the Helipad program.
**Modules**
Recognizing symptoms: explores signs and symptoms via a traffic light model (red, orange, and green indicators) of mental health. This module comprises an interactive map of the body that explains how we can recognize signs, symptoms, or indicators in our minds and bodies that tell us we might need to pay attention to our mental health and suggests what we can do about it.Seeking support: answers questions regarding how, where, and from which health professionals to seek help for mental health and how each provides assistance. Moreover, it demystifies the process of seeking help by providing a specific example pathway (ie, accessing a psychologist with or without a referral from a general practitioner [GP]) and 3 videos of health professionals (Employee Assistance Program, psychologist, and GP) explaining what they do to support people’s mental health.Treatment options: provides information regarding evidence-based treatment options including psychological treatment, medication, exercise, and lifestyle treatments for common mental health problems, such as depression and anxiety. The psychological strategies were focused primarily on strategies approved by the Australian Government Medicare Benefits Schedule (MBS [32]), which are the most accessible evidence-based treatments available through the MBS, such as cognitive behavioral therapy (CBT), with medical and lifestyle treatments suggested by members from the co-design group. Furthermore, this module contains a practical example of a specific CBT strategy called “cognitive restructuring,” works and an exercise on identifying people who may support them during challenging times.Helping others: explores how to help others in the workplace who may disclose their experiences of mental ill-health and provides some examples about how different responses to this disclosure can affect the outcome for the person experiencing a mental health issue. In addition, this module contains a video of a manager discussing their experience of an employee who disclosed their mental health issue.Supportive workplaces: addresses stigmatizing attitudes toward mental ill-health, help-seeking, and disclosure in the workplace. This module contains 3 videos of peers describing their experiences of disclosing in the workplace, myth-busting information in the form of a quiz on common mental disorders of depression and anxiety, and information targeting concerns about disclosure of mental ill-health in the workplace.

#### Active Control Program

The active control condition was chosen to maximize participant and organizational engagement in the trial and provide a strong test of the efficacy of the active ingredients of the Helipad program. The program comprises 5 time-matched standard written psychoeducation modules about mental health and well-being. The modules comprise written content from the National Institutes of Health News in Health newsletters [33] that was minimally edited by the research team (eg, to combine content from separate papers on the same topic). Written content focused on education on signs and symptoms of common mental health conditions of depression and anxiety disorders and how aspects of our lives (ie, sleep, exercise, relationships, and stress) impact our mental health. However, this program did not contain detailed information regarding treatment options, content explicitly targeting stigma reduction (eg, contact via peer stories), or how or where to seek help from health professionals. Furthermore, the content was not co-designed, is minimally interactive, and does not provide targeted information about help-seeking processes. Psychoeducation has been shown to increase mental health literacy and may have modest effects on reducing stigma but does not typically translate into changes in behavioral intentions such as help-seeking [24].

The modules are as follows:

1. Sleep and well-being: contains information regarding sleep, including sleep stages, sleep quality and duration, and how lack of sleep affects our overall health and well-being.

2. Exercise and physical health: provides information on how exercise is beneficial for health and well-being and tips on how to increase overall physical activity.

3. Mental health: provides information on depression and anxiety disorders, including signs and symptoms and how they can be treated.

4. Social relationships and health: explores how social relationships affect our health in both positive and negative ways and how social support may buffer stress.

5. Stress and health: provides information regarding stress, including the impact of stress on our physical and mental health and how we can reduce stress in daily life.

### Recruitment Procedures and Randomization

#### Workplace Recruitment

Recruitment of workplaces is expected to be conducted using our existing networks through the The Mental Health Australia General Clinical Trials Network. We plan to recruit approximately 30 to 36 workplaces, with 25 to 35 participants per workplace to meet our total sample size target of 900 adult participants. Workplaces will be eligible if they (1) report having at least 50 employees to ensure that each cluster is viable and (2) have an Employee Assistance Program (EAP) available for their staff to ensure that employees experiencing mental health concerns can access effective and immediate care. Any industry of work is eligible for inclusion. A mixture of general and high-risk workplaces (ie, those likely to be exposed to situations that may impact mental health, such as health care settings) initially in the Australian Capital Territory, New South Wales, and Victoria are being targeted. Recruitment is highly feasible based on previous public health trials conducted by the team (N=849 to 2773 [34-36]), and our universal cluster-based trials have typically recruited high numbers (eg, N=1477 [37] and N=1633 [38]).

We will invite workplaces through multiple channels, including directly via an email invitation addressed to the “key representatives” from a workplace such as managers or staff in charge of human resources, via telephone calls, and via invitation emails to employees in our existing networks. We will contact the workplace key representatives who express interest to determine organization characteristics and eligibility for the study.

#### Randomization

Given the cluster design, we will use a minimization approach to randomization [39]. Minimization is a type of randomization where the first participant (or cluster) is randomized and subsequent selections are allocated in a way that minimizes the imbalance on specific factors between groups. This method is helpful for a design with few participants (or clusters) and has the advantage of making each condition more closely matched on key factors across the trial. To implement this, we will use a preprogrammed computer algorithm that will assign each new workplace recruited into the trial into a condition. This process will aim to balance across conditions on the following key workplace characteristics: (1) workplace type (office-based vs non–office based), (2) organization size (<200 vs >200 employees), and (3) location (Australian Capital Territory or New South Wales or Victoria vs other Australian state or territory). Once a workplace has been allocated a condition, we will discuss with their key representative what participation in the trial involves and provide them with an email or SMS text message (depending on their preferred communication with employees) with an embedded link to their assigned study recruitment website. We expect the text to read as follows:

Would you like to participate in a research study testing a new resource for supporting employee wellbeing? Learn more about your mental health and wellbeing by completing a survey and a brief online program today: <link>.

We will ask the workplaces to send invitations to all their employees themselves, with each workplace determining who from within their organization will send this invitation. This process is designed to increase ecological validity, as the goal for the program is for it to be delivered by workplaces, we expect this to be a minimal burden (ie, 1 or 2 SMS text messages or emails) on the workplace administration staff tasked with sending invitations.

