### Data Analysis

An intention-to-treat approach to account for missing data of the mixed model repeated measures ANOVA (continuous data) or mixed effects logistic regression (binary data) will be used, adjusting for intraclass correlation to account for clustering effects within each site. Mixed models include all available data and account for within-individual variability, including those participants with missing data points, under the missing-at-random assumption [48].

Exploratory analyses will examine evidence for moderators or mediators of outcome and will be reported separately from the primary and secondary outcomes. Implementation outcomes at 6 months will be separately examined using description statistics, including *t* tests (2-tailed). The economic analysis will examine cost-effectiveness from the health sector and societal perspectives. The cost of the Helipad intervention and the active control program will be estimated using microcosting methods. Service use data will be limited in this study to health care professional visits or services accessed (internet program and helpline) specifically for mental health. The additional costs of health care resource use will be operationalized as the number of contacts with health professionals collected on the Actual Help-Seeking Questionnaire [49] (psychologist or counselor, psychiatrist, family doctor or GP, EAP, phone helpline, and internet-based treatment program). Lost productivity will also be evaluated in societal perspective costs as assessed through the WPAI questionnaire [47] and valued using the human capital approach. The ReQoL-10 Questionnaire [46] will be used to calculate utility values and quality-adjusted life years (QALYs) using the area under the curve method. Differences in costs between trial groups will be compared to the differences in QALYs through an incremental cost-effectiveness ratio (ICER) because of the inherent value-for-money connotations associated with cost-effectiveness ratios using QALYs. Additional ICERs using secondary outcomes will be calculated where the Helipad intervention is found to have an effect. Nonparametric bootstrapping will be used to determine CIs for ICERs.

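### As described, minimisation is deterministic after the first workplace, so the recruiting team could predict most allocations; a random element is needed

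*Protocol article*

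**What the plan says.** The protocol article (Randomization) states: "Given the cluster design, we will use a minimization approach to randomization". It explains that "the first participant (or cluster) is randomized and subsequent selections are allocated in a way that minimizes the imbalance on specific factors between groups", and that to put this into effect "we will use a preprogrammed computer algorithm that will assign each new workplace recruited into the trial into a condition". Three two-level factors are balanced: workplace type (office or not), size, and location. Size is written as "2) organization size (<200 vs >200 employees". The section mentions neither an allocation probability for later workplaces nor a rule for ties.

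Three other statements bear on who could use this information:

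- Workplace Recruitment: the study team contacts interested representatives to establish the organisation's characteristics and eligibility.
- Randomization: after allocation, the same team talks the representative through participation and supplies the link to the assigned website.
- Assessments and Blinding: the blinded parties are the participants (as far as possible), the analysing statistician and the self-completed assessments. Staff who recruit workplaces are not listed.

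**The concern.** Minimisation protects against selection only if the next allocation cannot be worked out in advance. Here the described rule puts chance into the first allocation alone. With three binary factors and workplaces entering one at a time, anyone who knows the earlier allocations and the new workplace's characteristics can compute the imbalance score for each arm. That person then knows the next assignment whenever the scores differ.

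At stake is allocation concealment at the level of the randomised unit. Someone who can foresee the arm could, even without intent, press harder for one workplace, delay another, or judge borderline eligibility differently. With only 30 to 36 workplaces, a few such decisions could make the arms differ in ways that the three factors do not capture. Concealment is also something a reader of the trial report will look for and, on this description, would not find.

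**Working it through.** The plan states no figure on this point, so there is none to reproduce. The rule as described was simulated instead.

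**Inputs from the protocol article**
- Number of workplaces K: 30 and 36 (Power and Recruitment).
- Three two-level factors; first workplace randomised, later ones sent to the arm that minimises imbalance (Randomization).

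**Assumptions, not in the documents**
- Workplace type and size each split 50:50.
- Share of workplaces outside the three named jurisdictions: 0%, 10% and 50%.
- Imbalance score for an arm = the sum, over the three factors, of the workplaces already in that arm that share the new workplace's level. Factors are weighted equally.
- The lower score wins; equal scores are broken at random. 4000 runs per setting.

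**Rule as described**

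| K | Share elsewhere | Fully determined | Guessed correctly | Mean arm-size difference |
|---|---|---|---|---|
| 30 | 50% | 0.771 | 0.885 | 0.26 |
| 30 | 10% | 0.775 | 0.888 | 0.265 |
| 30 | 0% | 0.793 | 0.897 | 0.06 |
| 36 | 50% | 0.777 | 0.888 | 0.265 |
| 36 | 10% | 0.781 | 0.891 | 0.244 |
| 36 | 0% | 0.796 | 0.898 | 0.068 |

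The guessing column follows from the determined share D: an observer is right on every determined allocation and on half of the ties, so P(correct) = D + (1 − D)/2. For K = 36 and 10% elsewhere this is 0.781 + 0.219/2 = 0.891. In counts, 0.775 × 30 ≈ 23 of 30 and 0.781 × 36 ≈ 28 of 36 allocations are fixed in advance.

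**With a random element.** The imbalance-reducing arm is chosen with probability 0.8, ties are random, and 10% of workplaces are elsewhere:

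| K | Scores unequal (U) | Guessed correctly | Mean arm-size difference |
|---|---|---|---|
| 30 | 0.827 | 0.749 | 0.903 |
| 36 | 0.835 | 0.750 | 0.88 |

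Check: P(correct) = 0.8U + 0.5(1 − U). For K = 30 this is 0.8 × 0.827 + 0.5 × 0.173 = 0.748; for K = 36 it is 0.8 × 0.835 + 0.5 × 0.165 = 0.751. Both agree with the simulation, and no single allocation is certain any longer.

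**Limits of these figures.** If ties were broken by a fixed rule, every allocation after the first would be determined. At the other extreme, if all three factors were constant, the rule would reduce to allocation in pairs: scores tie at every odd-numbered workplace, so half are determined and 0.5 + 0.5/2 = 75% are guessed. Strongly uneven factor splits could therefore give lower figures than those tabulated, but substantial predictability remains even in that limit.

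**The case against.** The strongest reply is that the quoted sentence is a general definition of minimisation. The trial's actual procedure is the computer program, whose probability and tie rule an article may leave to the full protocol. This stands in part: the article does not prove that the program is deterministic, and a reader should not infer that it is. But the article goes directly from the definition to the program as the way of carrying it out, and nothing elsewhere in the document supplies chance after the first workplace. The text does not merely omit a detail; it describes a rule in which only the first allocation is random.

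A second reply is that no text describes staff choosing the order or timing of enrolment by predicted arm. That is true. The point is that the opportunity exists, and the size of any resulting bias is not estimated here. The estimand is a change from preintervention, which would remove stable baseline differences in intentions. It would not remove differences in how readily workplaces respond to a program.

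Three stronger readings may tempt a reader, and the documents do not support them:

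- That the location factor is nearly constant. Recruitment is "initially in the Australian Capital Territory, New South Wales, and Victoria are being targeted", and the factor "3) location (Australian Capital Territory or New South Wales or Victoria vs other Australian state or territory" provides for other states. No expected split is given, and predictability hardly changes across the shares tried.
- That leaving out high-risk status is an error. The plan does seek "A mixture of general and high-risk workplaces" without balancing on it, but which factors to balance across 30 to 36 clusters is a design judgement, and workplace type may overlap with risk.
- That the analysis ignores the minimisation factors. Data Analysis describes "adjusting for intraclass correlation to account for clustering effects within each site" and gives no covariate list; such lists are commonly left to an analysis plan, which is not shown.

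**Conclusion.** The point holds for the allocation rule as published. It randomises the first workplace only, and it is operated alongside a team that knows both the inputs and the past results and is not listed as blinded. About 77–80% of allocations would be fully determined and about 89–90% guessable. This rests on even splits for type and size, equal factor weights and random tie-breaking. It is a weakness in concealment that should be corrected; it does not show that selection has occurred or that the program lacks a random element.

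The gap at exactly 200 employees is real but is only a slip in notation. It matters because a program needs a category for every workplace.

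**What to change.** - State that each workplace goes to the imbalance-reducing arm with a probability below 1, for example 0.8, and that ties are broken at random. If the program already does this, report the probability and the tie rule.
- Write the size factor as <200 versus ≥200 employees.

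The cost is one parameter and one inequality in the allocation program, ideally set before the first workplace is allocated. Balance becomes slightly looser: at 10% of workplaces elsewhere, the mean arm-size difference rises from about 0.25 to about 0.9 workplaces out of 30 to 36. In return, correct guesses fall from about 89% to about 75%.
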